## 7.3 Lost to Follow-Up

A participant will be considered lost to follow-up if we are unable to measure the secondary outcomes up to seven to thirty days from randomization including the need for surgical intervention (Y/N) or additional bleeding. At least 3 attempts will be made to follow up with the participants using contact information provided during the consent process.

# 8 Study Assessments and Procedures

## 8.1 Efficacy Assessments

The **primary feasibility outcomes** for the pilot trial are the enrollment rate (patients per site per month) and the proportion of patients receiving study drugs (at least 2 nebulized doses).  Safety is always an outcome, and all adverse events will be reviewed.

**The secondary outcome is** the ENT surgeon rationale, decision (Y/N) for the PTH patient to return to the OR, severity of bleeding with estimates of blood loss that include volume of hemorrhage recorded blood loss, and the number of blood transfusions. Additionally, we will determine the indirect local and systematic concentration of nebulized TXA by verifying our pulmonary physiologically based pharmacokinetic model. To verify the model, two lab samples will collect at opportunistic times either by finger stick or ad**. The study is not** powered for the secondary outcomes as this a pilot trial.

The **exploratory outcomes** will be age-appropriate pain scores and parent and child anxiety scales as measured by anxiety-state-trait scale (STAI). For children under eight years old their anxiety will be measured by STAI-C, which utilized pictures These will be exploratory as the pilot trial is not powered to determine the change in the outcomes.  Please see **Figure 7** for a timeline of all study procedures and outcomes.

## 8.2 Safety and Other Assessments

## 8.2.1 Safety OUTCOMES

Incidence of safety outcomes will be assessed at 1, 7 and 30 days after receipt of the study drug via a review of electronic health records and interviews. Specific, safety outcomes are thromboembolic disease: any venous or arterial thrombosis on standard diagnostic imaging post-randomization (including deep vein thrombosis, pulmonary embolism, sinus thrombosis, myocardial infarction, ischemic stroke) and seizures occurring within 24 hours (greater than 5 half-lives of TXA) of drugs documented by clinical or electroencephalogram.

## 8.2.2 HOSPITAL DATA COLLECTION and Patient-related OUTCOMES

**Electronic Health Record:** Data will be recorded for all enrolled patients to include age, sex, race and ethnicity, and chronic medical conditions. Upon presentation to the ED, we will also record vital signs and physical examination findings. We will collect baseline laboratory values from electronic health records that are routinely collected as the standard of care. Surgery-specific information will also be collected from electronic health records or charts including the type of tonsillectomy, description of photos of tonsillar bleeding, subject demographics (e.g., ethnicity), insurance, and clinical information. Moreover, a brief survey will be given to each attending ENT physician to document their rationale and concerns to go to the OR.

**Clinical Data Examples:** Should include the following, if collected per standard of care: vital signs (including height/weight), physical exam, upper airway and pulmonary exam, exam & findings as relating to OR use (e.g., photo of tonsillar bed), blood product usage, final hospital disposition. A recent height and weight of all patients should be collected from the electronic health record or from parents as body mass index (BMI) has been correlated with the severity of PTH.

Physician Survey: A post-operative survey will be distributed attending emergency and ENT physicians and staff that evaluate experience with patients PTH. The survey will be brief to have the physician detail the reasoning behind the decision to take the patient back to a second surgery or not. The remaining questions will be to describe the exam of the PTH in the operating room if performed. The surveys will be distributed electronically within 24 hours of randomization. The surveys will contain the following preamble “**[name], Associate Professor of Pediatrics at the University of Texas Health and Science Center, will be conducting a research study on Pediatric post-Operative Tonsillectomy hemorrhage. Participating is completely voluntary and participating or not participating in this research study will not affect an individual's academic or professional standing. Willing participants will be asked to complete this 10-minute survey that will be administered through a QR code or on paper. There will be no compensation for participating in this study. To protect your confidentiality, survey responses are anonymous, and no personally identifiable information will be asked. As an extra precaution, please do not write in information that could possibly identify you on the open-ended questions. If you have any questions, please reach out to [name] at [contact].**”

**Laboratory Data Examples** (collected if completed as the standard of care procedures): complete blood count, INR/Prothrombin time, activated partial thromboplastin time (aPTT), D-dimer, Thromboelastography, fibrinogen, and arterial or venous blood gas.

**Pharmacokinetic and Pharmacodynamic Testing:** Pharmacokinetics samples will be collected after completion of the last nebulized treatment received within sixty minutes. A second time point should then be collected after sixty minutes up to eight hours from last nebulization, separated from the previous time point by at least sixty to ninety minutes. The results from the TXA level measurements will be used for research purposes only and not be available to clinicians. The serum TXA levels will be used to develop a TXA PK model and determine the population variability. We will develop a base model to determine a best-fit compartmental model, distribution, and elimination kinetics. We will also use stochastic models to evaluate between-subject variability in PK parameters. Serum TXA concentrations will use 200 microliters of plasma measured by an ultra-high performance liquid chromatography tandem mass spectrometry method specifically developed for sensitive and precise analysis of low TXA concentrations at the U.S. Army Institute for Surgical Research. Moreover, we will use the remaining 200 microliters to measure pharmacodynamics effects of nebulized TXA in the plasma. ELISA can use minimal plasma volume (<300 μL) to run commercial kits measuring Plasmin-antiplasmin (PAP) complexes, D-dimer, Thrombin-antithrombin (TAT) complexes, Prothrombin fragment F1+2 (F1+2), and Plasminogen activator inhibitor-1 (PAI-1). Combination of pharmacokinetic and pharmacodynamic effects achieves the primary goal to determine drug systematic compared to local effects.

The protocol will adhere to the following guidelines when scheduling procedures to collect pharmacokinetic samples:

- Samples will be collected in EDTA 1 mL tubes (Fisher Scientific Catalog number 22-030-402). Within 2 hours of sample collection, tube will spin in a calibrated centrifuge. Please see attached centrifuge calibration standard of operating procedure.
- Centrifuge procedures consist of:
  - Place sample in centrifuge with appropriate weighted balance
  - Centrifuge sample at 2500 RPM for ten minutes at room temperature
  - Remove sample from centrifuge, using a pipette remove plasma above buffy coat and place into a clean Eppendorf tube (roughly 0.4-0.6 mL).
  - Place Eppendorf tube back in centrifuge with appropriate balance.
  - Centrifuge second time at 2500 RPM for ten minutes at room temperature.
  - Remove sample from centrifuge, using a pipette to remove 7/8^th^ of sample and aliquot equally into two labelled cryovials (roughly 0.2 mL). Each vial will be labelled with participant enrollment number, date and time of collection, and either “TEAPOT PK” or labeled “TEAPOT PD”.
  - Store samples in -70°C to -80°C freezer.
- All sample shipments will follow IATA and cold-chain management guidance.
- Specimens submitted frozen can be collected on any day but must be stored frozen and shipped to the U.S. Army Institute of Surgical Research on Monday through Thursday. If frozen specimens cannot be shipped immediately, they must be maintained in a -70°C to -80°C freezer per cold-chain-management procedures.
-
[figure not shown]
Fresh blood specimens may be collected, processed, frozen and shipped Monday through Thursday during normal business hours.

**Figure 5:** Timeline of Study Procedures (*at least six minutes after last neb) STAI is the State-Trait Anxiety Inventory to be administered to participants and guardians. *AEs will be collected through a phone call at 30 days +/- 5 days*

Coded specimens with dates will be sent to University of Utah and/or U.S. Army Institute of Surgical Research for pharmacokinetic analysis. Please see Figure 5 timelines of events.

**Blood product transfusion volume and Blood Loss:** Blood product transfusion volume will be measured at discharge or 24 hours (whichever comes first). This will include the volume of packed red blood cells, platelets, plasma, cryoprecipitate, or whole blood. Any mention of blood loss in electronic health records from emergency, anesthesiology, or surgeons’ notes will be recorded.

**Hospital Discharge Information:** Information will be collected after hospital discharge including otolaryngologist (ENT) notes and physical exam documentation, hospital discharge date and time, destination upon discharge, and mortality.

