# 3 Objectives and Endpoints

| OBJECTIVES | ENDPOINTS | JUSTIFICATION FOR ENDPOINTS |
| --- | --- | --- |
| Primary | | |
| Evaluate the feasibility to enroll 0.6 patients/site/month  Nebulize at least two of three doses of TXA to children with PTH.  Determine the local and systematic concentrations of nebulized TXA in children  Determine incidence of adverse and serious adverse events | Enrollment after one year and % of nebulization’s. Go/no-go threshold is 0.6 patients per site per month for a total of 22 patients. Time and success to obtain consent will establish need for exception for informed consent (EFIC).    The goal is >90% of patients will receive at least two of three planned nebulization of TXA.  Collection of two blood samples from each participant. This will verify a pulmonary physiological-based PK model (PBPK) (i.e., nasal cavity, pharynx, and lung) that indirectly predicts the oropharyngeal and systematic concentration of nebulized TXA.  A phone call or email will be placed to participants at 30 +/- 5 days. | The overall incidence of PTH is 5%, yet numbers per site may be very different. Assessment and consent will optimize site selection, recruitment process, and the plan the main trial.    The establishment of a pragmatic protocol design will help design a large trial.  Limited data on nebulized TXA systematic absorption. Topical PK studies of TXA document a significant reduction in systematic levels but the same hemostasis effect.  Safety Evaluation as recommended by the FDA. |
| Secondary | | |
| Determine the number and rationale for PTH patients to return to the OR; and    Determine the number of blood transfusions and estimated blood loss and      Determine the recurrence of PTH after TXA, saline, or return to the OR. | Collection number participants and surveys on ENT surgeons’ decision to go to the OR    Collection of electronic health record data on number of blood transfusions and estimated blood loss    Survey families to determine PTH recurred seven days from randomization. | To evaluate if return to the OR can be an outcome for the main trial.    To evaluate if TXA decreased severity of PTH bleeding.      To evaluate if TXA or return to OR prevented PTH recurrence. |
| Tertiary/Exploratory | | |

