## 6.4 Study Intervention Compliance

Every week of the study enrollment, study staff will review and complete data entry for patients screened or missed eligible patients. All relevant surgical and clinical data will be collected related to risk factors for PTH, pharmacokinetics, or receipt of study drug or placebo (please see the schedule of activities). Relevant data collection for enrolled PTH patients includes BMI, historical platelet counts, episodes of bleeding or clotting, insurance, ethnicity, surgical tonsillectomy technique performed, prescribed and over the counter medications, and other data as will be described in the manual of operations. Data collected on missed eligible patients, using a waiver of consent, will be age, sex, height, and weight if available, medications taken upon admission, insurance, and outcomes including surgery performed or not. For more details see the Manual of Operations. Data will be collected and managed using REDCap hosted at the University of Utah. REDCap (Research Electronic Data Capture) is a secure, web-based application designed to support data capture for research studies. Below is a table of associate responsibilities.

| **Procedure** | **Data Source** | **Responsible** |
| --- | --- | --- |
| Screening and eligibility | Electronic Health Record (EHR) | Research Staff* |
| Medical History | EHR or study staff | Clinical and Research Staff |
| Consent | E-consent, Virtual, or in Person | Research Staff |
| Demographics/baseline information | EHR or study staff | Clinical and Research Staff |
| Concomitant medication review | EHR | Clinical and Research Staff |
| ED/Hospital admission data collection | EHR | Clinical and Research Staff |
| Administer study nebulization 1 | EHR or study staff | Clinical and Research Staff |
| Administer study nebulization 2 | EHR or study staff | Clinical and Research Staff |
| Administer study nebulization 3 | EHR or study staff | Clinical and Research Staff |
| Surgical Hemorrhage Control? (Y/N) | EHR or study staff | Research Staff |
| 1st TXA Level (last neb up to 60 mins) | Blood Sample | Clinical and Research Staff |
| 2nd TXA Level (60 mins to 8 hours) | Blood Sample | Clinical and Research Staff |
| Process, Freeze, Store and Ship | Plasma Samples | Research Staff |
| ENT Surgical Decision Survey | ENT Surgeon | Research Staff |
| Age-Appropriate Pain Scale | EHR, Text, or Phone | Research Staff |

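### Section 8.2.2 contradicts the rest of the protocol on who supplies the OR-decision rationale, and allows the reason to be recorded after the operative findings are known

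*Protocol*

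**What the plan says.** The Physician Survey paragraph of section 8.2.2 is the only place that describes the content and delivery of the survey. On recipients it says: "A post-operative survey will be distributed attending emergency and ENT physicians and staff that evaluate experience with patients PTH". It asks for the reasoning behind operating or not operating, and then adds: "The remaining questions will be to describe the exam of the PTH in the operating room if performed". On timing: "The surveys will be distributed electronically within 24 hours of randomization". The preamble tells respondents that "survey responses are anonymous, and no personally identifiable information will be asked".

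The Electronic Health Record paragraph of the same section gives a narrower recipient: "a brief survey will be given to each attending ENT physician to document their rationale and concerns to go to the OR". The responsibilities table in section 6.4 has the row "ENT Surgical Decision Survey | ENT Surgeon | Research Staff", which names the ENT surgeon as the only data source. The synopsis (section 1.1) and section 3 define the endpoint through surveys on the ENT decision. The Schedule of Activities (section 1.3) lists an ENT decision survey under Day 0-1, and section 8.1 names the ENT surgeon's rationale as a secondary outcome.

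Section 3 gives the purpose of the endpoint: "To evaluate if return to the OR can be an outcome for the main trial".

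**The concern.** Two features of the Physician Survey paragraph work against that purpose.

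The first is who answers. An emergency physician or a member of staff can report an impression of why a child went to the OR, but the endpoint is the reason held by the surgeon who decided. With several groups invited, anonymous returns and no stated role field, the protocol gives no way to pick out that surgeon's answer.

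The second is when the reason is recorded. To judge return to the OR as a trial outcome, one needs to know why surgeons go before they have looked. The protocol's own background (section 2.2) describes a treated child who was taken back and found to have stopped bleeding, so decision and finding can diverge. A reason written on the same form as the operative examination may be coloured by what was found. A child who was not operated on has no such findings.

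At stake is the usefulness of a descriptive pilot endpoint for choosing the phase 3 outcome. No efficacy conclusion of the pilot depends on it.

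**Working it through.** No planned figure is in dispute, so the check is a comparison of the texts plus one illustrative multiplication.

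**Who supplies the reason**

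| Place in protocol | Source named |
|---|---|
| 1.1 Synopsis; 3 Objectives and Endpoints | Surveys on the ENT decision |
| 1.3 Schedule of Activities | ENT decision survey |
| 6.4 responsibilities table | ENT surgeon |
| 8.1 Efficacy Assessments | ENT surgeon's rationale |
| 8.2.2 Electronic Health Record | Each attending ENT physician |
| 8.2.2 Physician Survey | Attending emergency and ENT physicians, and staff |

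The last row is the outlier. The direct conflict over recipient or source is with 6.4 and the other paragraph of 8.2.2. The remaining rows define the endpoint or name the survey in ENT terms. No place says that emergency or staff answers count toward the endpoint, and none says that they are kept out of it.

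**When the reason is recorded**

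1. The survey is labelled post-operative.
2. One form asks for the reason and, where an OR examination took place, for its findings. The findings items can be completed only after that examination.
3. The 24-hour rule limits when the survey is sent out. It does not require the reason to be given before surgery.
4. If post-operative is read as meaning after the tonsillectomy, steps 2 and 3 are unchanged.

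For operated children the protocol therefore permits a reason given after the findings are known.

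**How many children this could touch**

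Inputs: 12 children at the single site, 6 per arm, and 73% historically going to the OR at San Antonio (all section 5.5).

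- Historical share in both arms: 12 × 0.73 = 8.8, about 9 of 12. About 3 would have no operative findings.
- 73% in the saline arm and the 61% TXA planning rate of section 9.2: 6 × 0.73 + 6 × 0.61 = 4.4 + 3.7 = 8.0.
- 73% in the saline arm and the 36.1% reported for TXA-treated patients in the larger retrospective study in section 2.2: 6 × 0.73 + 6 × 0.361 = 4.4 + 2.2 = 6.5.

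The range is roughly 6.5 to 9 of 12. The last two lines combine rates from different sources and only show how far the first could fall. All three assume a completed survey for every operated child and surgery before completion. Section 8.2.4 follows return to the OR for seven days, so some operations may come after the form was filled in.

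**The case against.** The strongest reply is that the endpoint is clear. Five sections and the other paragraph of 8.2.2 speak of ENT, and only someone who was in the OR can answer the findings items, so the wider recipient list may be loose drafting. The form itself is not shown, section 6.4 leaves detail to the manual of operations, and a promise not to ask for identifying information does not rule out a role item. This stands as far as it goes: the documents show a contradiction about respondents and a missing rule, and they do not show that answers will be pooled.

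Three stronger readings are tempting, and the documents support none of them.

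- A reader might infer that most rationale responses will come from people who did not decide. The survey is voluntary and the number of respondents per child is not stated, so no share can be given.
- A reader might infer that the unit of analysis is wrong. The protocol fixes no unit or test for these responses, section 9.4.1 makes the analysis descriptive, and handling of multiple responses may be left to the SAP.
- A reader might infer that hindsight makes decisions look better founded. A surgeon who found a dry tonsillar bed could equally report a weaker reason.

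The survey is also not the only record. Whether surgery took place is captured from the health record or study staff (sections 1.3 and 6.4), and ENT examination findings and notes are collected separately (section 8.2.2). These show what was done and found, but they do not secure a reason given before the findings.

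Finally, requiring a form before OR entry has a real drawback. Being asked to justify the decision might alter it, it adds burden in an emergency, and section 6.1.1 says that the study drug is the only change to ED management. That objection stands, and the fix does not make such a form mandatory.

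**Conclusion.** The point holds as a contradiction about who answers and a gap about when. Followed as written, the Physician Survey paragraph yields anonymous answers from several groups with no stated way to isolate the deciding surgeon's reason. Pooling is possible but is not stated. For operated children the reason may be recorded after the operative findings are known. That could affect up to about 9 of 12 children in the single-site study if the historical 73% applied in both arms, and fewer if TXA lowers the OR rate or if some surgery follows completion of the form. The size and direction of any resulting bias are unknown.

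The consequence is limited to a descriptive, unpowered secondary endpoint. It still merits correction, because that endpoint is meant to inform the choice of the main-trial outcome and the reason at the time of the decision cannot be recovered later.

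**What to change.** In the Physician Survey paragraph of section 8.2.2:

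1. Define the rationale endpoint as one response per enrolled child, from the ENT surgeon who made the decision to operate or not, in line with sections 1.3, 3, 6.4, 8.1 and the Electronic Health Record paragraph of 8.2.2.
2. Add an item for the respondent's role. If emergency physicians or staff are still surveyed, report their answers separately and outside the endpoint.
3. Place the rationale items ahead of, and separate from, the operative-findings items. Record whether the reason was given before or after the OR examination, with capture at the time of the decision where this does not interfere with care.
4. State the anonymity wording so that it is compatible with one response per child and a recorded role.

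The cost is protocol wording and a slightly longer or split form. Some reasons will still be given after surgery, but they will be identifiable as such.

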Nebulization of TXA is not a common route of administration compared to oral or intravenous delivery. Inhaled or intranasal medication can be rapidly absorbed across the large surface area of the respiratory tract epithelium. Some drugs absorbed into the pulmonary circulation enter directly into the systemic circulation via the pulmonary vein, possibly bypassing first-pass metabolism that occurs with oral drugs. Previous research into the site of action for inhaled medications has been limited to animal studies because biopsy of the entry site would be dangerous to the subject. However, to choose the optimal dose it is important for investigators to understand the level of absorption at the topical and systematic level. Typical pharmacokinetics of TXA cannot be done in this study, however the concentrations can be estimated by verifying physiologically based pharmacokinetic (PBPK) model designed to predict the change in pharmacokinetics that occur as the inhaled drug cross the respiratory epithelium. A pulmonary PBPK model begins with extracting from the literature all known pharmacokinetic data on the inhaled drug and the known properties for absorption and metabolism across the respiratory epithelium. Fortunately, several pharmacokinetic studies using healthy adults or animals have been performed with TXA. Additionally, several pediatric and inhaled pharmacokinetic studies are available. Utilizing this data, we can build a PBPK model to predict the level of topical and systematic absorption. The main advantage of this method is to understand how an inhaled drug is absorbed and metabolized in the respiratory epithelium with the fewest number of systematic samples. Instead of collecting a wide range of samples from different ages and doses, we only need a few samples to verify that the parameters used to build the model were correct. This technique has been used in multiple studies to predict the dosing response in various populations or using different routes of administration.

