# 9 Statistical Considerations

## 9.1 Statistical Hypotheses

The pilot study is not designed to test an efficacy hypothesis, but rather to determine the feasibility for patient enrollment and the number of doses received per patient.

**Our primary hypothesis** for the single site and the multi-site study is that we can enroll at least 0.6 patients per site per month and deliver a minimum of two out of three planned nebulized TXA doses to >90% of enrolled patients.  The single site study will only be one year and the multi-site study for 18 months. We will test each of this (yes/no) hypothesis using a Mantel Haenszel test stratified by site for a total of 12 patients for the single-site study for greater than 24 nebulization and for the multi-site study up to 22 patients with greater than 44 nebulization's recorded as delivered.

**Our secondary goals** will be to determine if nebulized TXA prevents going to the OR for PTH and utilization of blood products. These goals are not powered to be tested in the pilot study. **Our second aim** is to verify a pulmonary physiological based pharmacokinetic (PBPK) model (i.e., nasal cavity, pharynx, and lungs) will predict the change in the area under the curve (AUC0-α) of TXA concentration in systemic compartments with accuracy (average absolute fold error <2) and precision (average fold error <2). We will calculate the AUC of accuracy and precision of the model using the linear trapezoid rule. For the PBPK model, we will use previously published PK data to construct the model before verifying it with systematic samples.

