### 9.4.3 Analysis of the Secondary Endpoint(s)

Our primary secondary outcome is to select the PBPK model that best characterizes the data using individual and population acceptance criteria. To apply the acceptance criteria, we will simulate plasma drug concentrations for everyone using the PBPK model and will compare predictions with observed concentrations. We will assess model bias by calculating the average fold error between predicted and observed concentrations: AFE=10[1/N∑log(predicted/observed)]. The AFE indicates model under- (AFE<1) or over-prediction (AFE>1) when compared with observed values of the individual. We will assess model precision by calculating the absolute average fold error: AAFE= 10[1/N∑|log(predicted/observed) |] for each curve. We will consider <30% bias (AFE 0.7–1.3) and ≤2-AAFE reasonable predictions. We will assess population predictability by generating a prediction interval (5th to 95th percentile) of drug concentrations per time point for the population and quantifying the number of observed concentrations that fall outside of the prediction interval. The model will be accepted if 90% of observed concentrations fall within the prediction interval.

Differences in exploratory outcomes will be analyzed by unpaired t-tests (for ratio measures such as blood loss) or by Mann-Whiney tests (for ordinal measures such as parental anxiety scale). However, the pilot study is not designed to determine a difference in these outcomes but to determine the feasibility and procedures of the main trial.

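### The protocol gives the TXA samples conflicting roles (verify, develop, select), so acceptance of the PBPK model need not be an external verification

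*Protocol*

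**What the plan says.** The protocol describes the use of the TXA concentrations in three ways.

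- **Verify only.** Section 9.1: "we will use previously published PK data to construct the model before verifying it with systematic samples". Section 2.2: "we only need a few samples to verify that the parameters used to build the model were correct". Section 4.2 likewise says a small number of samples is needed only for verification.
- **Develop.** Section 8.2.2, under pharmacokinetic and pharmacodynamic testing: "The serum TXA levels will be used to develop a TXA PK model and determine the population variability". It continues: "We will develop a base model to determine a best-fit compartmental model, distribution, and elimination kinetics", and "We will also use stochastic models to evaluate between-subject variability in PK parameters". It does not say whether this compartmental model is the PBPK model or a separate one. Section 2.1 also names outside data and trial samples together for both building and verifying a model.
- **Select.** Section 9.4.3 states the outcome as to "select the PBPK model that best characterizes the data using individual and population acceptance criteria". The criteria are AFE between 0.7 and 1.3, AAFE of at most 2, and 90% of observed concentrations inside the 5th to 95th percentile prediction interval. The section names no held-out data and no locking of the model before the levels are used.

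On feasibility, section 2.2 says: "Typical pharmacokinetics of TXA cannot be done in this study". Sections 1.3 and 3 plan two samples per participant, both after the last nebulization.

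**The concern.** A model built in advance and then compared with new concentrations is tested externally. A model fitted to those concentrations, or kept because it fits them best among several, is not, because the data that chose it also judge it. Section 9.4.3 is the operative analysis section and it concerns the PBPK model itself, so its wording cannot be put down to a side analysis.

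Section 4.2 expects the verified model to be able to set the phase 3 dose. A model reported as verified when it was selected on the verifying samples would carry more authority into that decision than the data give it.

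A related concern is that section 8.2.2 promises compartmental structure, distribution and elimination kinetics, and between-subject variability. That is a large set of outputs for two samples per child, and it sits badly with the protocol's own statement in section 2.2.

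**Working it through.** The protocol gives no sample size or precision figure for the PK aim, so there is no figure of its own to reproduce.

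**Data available.** Allocation is 1:1 (section 4.1), and only TXA-arm samples inform the model.
- Single site: 12 / 2 = 6 children, 6 × 2 = 12 concentrations (section 5.5).
- Multi-site: 22 / 2 = 11 children, 22 concentrations (section 9.2).

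**Step 1: tuning a scale term.** Section 9.4.3 defines AFE = 10^[mean of log(predicted/observed)]. If one scale factor, such as the absorbed fraction, is fitted so that the mean log error is zero, AFE = 10^0 = 1.00. The 0.7 to 1.3 bias check then cannot fail. This needs no assumption about TXA.

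**Step 2: choosing among candidates.** Assumed inputs, none from the protocol: between-subject log SD 0.5, residual log SD 0.2, and candidate-model bias on the log scale with mean 0 and SD ln 2. The prediction interval is taken as correctly sized: half-width 1.645 × √(0.5² + 0.2²) = 1.645 × 0.539 = 0.886 on the log scale. The candidate with the lowest AAFE is kept. Wrong acceptance means the kept model passes although its true bias lies outside 0.7 to 1.3. Results from 40,000 replicates with 6 children × 2 samples:

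| Candidates | Pass AFE and AAFE | Pass all three criteria | Wrong acceptance, all three |
|---|---|---|---|
| 1, locked | 33% | 22% | 4.8% |
| Best of 5 | 82% | 55% | 11.5% |
| Best of 10 | 93% | 63% | 12.3% |

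The pass rate rises by 55/22 = 2.5 times and 63/22 = 2.9 times. With 11 children the three-criterion rates are about 20%, 53% and 61%. If the scale is refitted outright, all three criteria are met in about 75% (6 children) or 69% (11 children) of runs.

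Sensitivity, AFE and AAFE only, 6 children: with between-subject log SD 0.3, 34% for one locked model against 86% for the best of 5; with 0.7, 25% against 66%.

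**Step 3: why the coverage rule matters.** Meeting 90% of 12 observations requires at least 11. For a perfectly calibrated interval and independent observations, P = 12 × 0.9^11 × 0.1 + 0.9^12 = 0.377 + 0.282 = 0.66. For at least 20 of 22 it is 0.62. This rule therefore limits acceptance even of a good model.

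**Step 4: what two samples per child support.** One compartment with absorption has three parameters per child (ka, CL/F, V/F) and two compartments have five, against two concentrations. A child's own parameters are not identifiable. A two-compartment population model needs about 8 parameters (5 fixed, at least 2 variances, 1 residual) from 12 or 22 observations.

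A 400-run simulation of a pooled one-compartment fit (assumed ka 2/h, k 0.35/h, residual log SD 0.2, between-subject log SD 0.3 to 0.5) gave these 5th to 95th percentile ranges:
- 6 children: ka about 0.7–11 (SD 0.3) or 0.7–100 (SD 0.5); k about 0.18–0.77 or 0.12–0.93.
- 11 children: ka about 0.8–5 or 0.7–10; k about 0.22–0.75 or 0.17–0.89.

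Typical values can be estimated, but poorly.

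**The case against.** The strongest reply is that section 9.1 states the intended order: published data first, trial samples second. Section 8.2.2 never mentions PBPK in its modelling sentences and may describe a separate population analysis. Running such an analysis on the same samples would not spoil an external PBPK check. Section 9.4.3 gives no number of candidates and describes no refit, and details of a model lock could sit in an analysis plan that is not shown.

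Much of this stands. Circularity is not the declared plan for the PBPK model, and the AFE = 1.00 result applies only if something is fitted. But the selection wording in section 9.4.3 is a stated rule about the PBPK model, not a missing detail. Section 9.1 does not cure it, because several literature-built candidates could still be chosen on the trial samples and then declared verified on them.

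Three stronger readings are tempting and are not supported:
- **That the model would nearly always be accepted.** Rates of 82% to 93% appear only if the 90% coverage rule is left out. With it they are 55% to 63%.
- **That selection makes accepted models less trustworthy.** The share of accepted models that are wrong hardly changes: 4.8/22 = 22% for one locked model and 12.3/63 = 20% for the best of 10. What rises is how often a wrong model is accepted overall.
- **That the section 8.2.2 parameters cannot be derived.** This is true for each child separately. A pooled or mixed-effects fit, especially with literature priors, can give imprecise typical values.

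It is also fair to note that the PK aim is listed as primary in sections 1.1 and 3 but secondary in sections 8.1 and 9.4.3.

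**Conclusion.** The point holds as an unresolved contradiction plus a selection step that permits circularity. It does not show that the planned verification is circular. As written, a reader cannot tell whether acceptance under section 9.4.3 would be a test of a model fixed in advance or of one chosen on the same samples.

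If it is the latter, acceptance is inflated about 2.5 to 3 times and wrong acceptance goes from about 5% to about 12% with 6 TXA children. These sizes rest on the assumed variability, candidate bias, number of candidates and a correctly sized interval. The text conflict and the AFE = 1.00 result do not. The distribution kinetics and between-subject variability promised in section 8.2.2 would be weakly supported by 6 to 11 treated children. The wording should be changed before any TXA level is analysed.

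**What to change.** - **Section 9.4.3:** replace the aim to "select the PBPK model that best characterizes the data using individual and population acceptance criteria" with a statement that one PBPK model, built from published data as in section 9.1, is locked and archived before any TXA level is released to the modeller. State that the acceptance criteria are applied once to that model, and that any refit or model choice using trial samples is exploratory and is not called verification.
- **Section 8.2.2:** state that the compartmental and between-subject-variability modelling is separate from the PBPK verification and exploratory. It need not be deleted.

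The cost is wording in two sections and an archived model file. The downside is that the locked model may fail its criteria, and a later refit would then not count as verification.
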